## Abstract

**Background:**

There is a need for assistance from primary care mental health workers in general practice in the Netherlands. General practitioners (GPs) experience an overload of frequent attenders suffering from psychological problems. Problem Solving Treatment (PST) is a brief psychological treatment tailored for use in a primary care setting. PST is provided by nurses, and earlier research has shown that it is a treatment at least as effective as usual care. However, research outcomes are not totally satisfying. This protocol describes a randomized clinical trial on the effectiveness of PST provided by nurses for patients in general practice. The results of this study, which currently being carried out, will be presented as soon as they are available.

**Methods/design:**

This study protocol describes the design of a randomized controlled trial to investigate the effectiveness and cost-effectiveness of PST and usual care compared to usual care only.

Patients, 18 years and older, who present psychological problems and are frequent attenders in general practice are recruited by the research assistant. The participants receive questionnaires at baseline, after the intervention, and again after 3 months and 9 months. Primary outcome is the reduction of symptoms, and other outcomes measured are improvement in problem solving skills, psychological and physical well being, daily functioning, social support, coping styles, problem evaluation and health care utilization.

**Discussion:**

Our results may either confirm that PST in primary care is an effective way of dealing with emotional disorders and a promising addition to the primary care in the UK and USA, or may question this assumption. This trial will allow an evaluation of the effects of PST in practical circumstances and in a rather heterogeneous group of primary care patients. This study delivers scientific support for this use and therefore indications for optimal treatment and referral.

## Background

In primary care the prevalence of psychological problems (e.g. depression, anxiety, stress, somatization, unexplained or functional symptoms) ranges from 30% to 70%. Patients with these complaints, symptoms or disorders frequently visit their general practitioner [1] and only 3% of all patients are referred to a specialist. This implies that mental health care is a core activity in primary care [2]. For many of these complaints and symptoms no evidence-based treatment is available [3]. There is a clear need for an effective treatment for common mental disorders in primary care.

### Problem Solving Treatment(PST) in primary care

In 1971 D'Zurilla and Goldfried published a theory in which problem-solving was defined as a cyclic process in five stages: problem orientation; problem definition; generation of alternative solutions; decision making, and solution implementation and was called problem solving therapy [4]. Since then, problem solving therapy has been applied for a wide range of psychological problems in all kinds of areas. In 1995 Gath and Mynors-Wallis conducted an experiment based on a basic form of PST in primary care. This is strictly protocollized and based on the principles of cognitive behavioral therapy (CBT) [5]. The treatment is brief and focuses on practical skill-building. It consists of a maximum of six sessions, each of which contains seven steps of problem-solving (see Figure 1) which are applied in a systematic manner towards problem resolution. The rationale is that it increases the patient's understanding of the relationship between everyday problems and psychological symptoms. The goal of PST is to help patients to regain control of their lives.

**Figure 1 F1:**
[figure not shown]
The seven stages of problem solving treatment.

There is evidence that PST can be an effective way of helping patients, and in particular patients with depression, to deal with psychological problems. One earlier study showed the superiority of PST over placebo but no superiority over amitryptiline [6]. A second study showed equal results in clinical outcomes between patients who received PST and patients who received usual care from their GP [6]. When community nurses provided PST the results were the same as for usual care from the GP, but the economic evaluation was more positive for the PST group [7]. Patients with minor depression who received PST showed the same improvement as patients who received a placebo, but their symptoms improved somewhat more rapidly than those of patients who received a placebo during the latter treatment. Patients with dysthymia who received PST and paroxetine showed significantly more improvement than patients who received a placebo [8]. Compared to other GP interventions there is good evidence PST is effective for major depression [1].

### PST provided by nurses as a potential option

Patients with psychological problems need more time than is available in general practice. The usual 10-minute consultation with a GP is generally too short to explain and explore these psychological problems. To complicate matters more, these problems are often interwoven with physical issues such as fatigue and sleeplessness. Furthermore, patients are ambiguous in presenting their symptoms [9]. Given this fact, in combination with the high prevalence of psychological problems in primary care, treating these patients will result in a shift of tasks to nurses. Especially nurses who are skilled in working with psychiatric patients, may become indispensable in primary care [10]. Nurses can be successfully trained in the techniques of PST and can provide effective PST for primary care patients [11]. Recent results show that a CBT protocol for panic-disorder can adhered by a therapist with minimal of or no CBT experience [12].

There are several issues which stimulate further investigation. First, PST may be the way forward in the Netherlands, where GPs have a heavy workload and patients need better tailored collaborative forms of care, focused on self-help and education.

There are still very few nurses working in Dutch general practice and although preliminary experiments are taking place to enhance and define the role of nurses in primary care, PST could be a welcome innovation in their task profile. So, innovative projects in primary care in the Netherlands are needed.

Secondly, there is a lack of research outcomes on the effectiveness of talking treatment for anxiety symptoms in patients. In this trial, patients with depressive as well as anxiety symptoms will be included. Only one study has reported substantially better outcomes for primary care patients with panic disorder, who received CBT and pharmacotherapy from a therapist with minimal or no CBT experience, like a nurse, than patients with usual care only from their GP [12].

Third, PST in primary care could prevent or stimulate a referral to secondary care for patients with complaints which cannot be treated in primary care. This would also stimulate better tailored collaborative forms of care and prevent the deterioration of complaints.

The primary aim of the present trial is therefore to investigate whether PST for patients with psychological problems provided by nurses in primary care, is effective.

## Methods

### Design

A randomized, controlled trial is being carried out to evaluate the effects of PST. At least 160 primary care patients will be included; 80 will receive usual care and PST and 80 will receive usual care only. At baseline, after the intervention and after 3 and 9 months the patients will be asked to fill in a questionnaire, and at baseline and after 9 months they will be asked to cooperate in a (diagnostic) telephonic interview. Primary outcome is the reduction of symptoms, and other outcomes measured are improvement in problem solving skills, psychological and physical well being, daily functioning, social support, coping styles, problem evaluation and health care utilization.

The Medical Ethics Committee of the VU Medical Center in Amsterdam approved the study design.

### Study population

The study population will consist of Dutch-speaking adults (18+) who visited a participating GP more than three times in the last six months. To asses whether psychological problems are present, the General Health Questionnaire 12 item version (GHQ-12) will be used for screening [13]. At random we visited the participating GP practices to ask patients to fill in our screening questionnaire while they where waiting to see their GP. If they had a score negative score on more then three out of twelve questions (indicating the presence of psychological problems) and if they were willing to participate, they were included. Patients were excluded from the study if they: received any treatment in mental health care; suffered from a severe (psychical) disease or personality-disorder; accepted no other explanation for their complaints than a somatic rationale; and patients with an non-consistent medication for anxiety or depression. Patients with severe drug addictions, suicidal wishes or mental retardation were excluded. An external researcher conducted block-randomization, so the allocation was concealed.

#### Intervention: usual care and PST provided by nurses

Consistent with earlier research on PST training skills [11], the nurses in this RCT were trained for two days by experienced supervisors who were also members of the original Oxford research group[6]. The nurses were closely supervised by means of video and audiotapes. A CBT supervisor will carry out supervision after the training, for one hour every three weeks. The nurses will deliver audiotapes and PST protocol forms to the supervisor. Consistent with advice in earlier research [11] before the nurses started treating patients in the trial, they treated four patients to practice their problem-solving skills after the training. The patients are also seen by their GP for general health management if necessary.

#### Usual care: health management provided by the GP

The consult is intended to be as natural as possible so that the GP will not influence the quality of the usual care provided. Many GPs use the guidelines issued by the Dutch College of General Practitioners [14]. The guidelines for psychological complaints such as anxiety and depression describe management options as (anti-anxiety of anti-depressant) medication and/or 'watchful waiting' if a referral seems unnecessary [15].

### Outcome measures

#### Primary outcome: reduction of symptoms measured with the HADS

The Hospital Anxiety and Depression Scale (HADS, [16]) is used to monitor symptom levels of anxiety and depression in the study population. The questionnaire consists of 14 items to which answers can be given on a 4-point scale (0–3). The HADS is considered to be unbiased by coexisting general medical conditions, and changes in HADS scores can therefore be used to calculate an objective effect size of the treatment provided (calculations described in 'Sample size'). In the Dutch validation of the HADS [16] the primary care patients have a mean of 6.2 (SD 3.8)for anxiety and 3.7(SD 3.4) for depression with a total mean of 9.9 (SD 6.1). Reliability for these patients is a Cronbach's alpha of .82 for the total score. The HADS is found to perform well in assessing the severity of symptoms [17].

#### Secondary outcomes: reduction of symptoms measured with the PHQ

The Patient Health Questionnaire (PHQ) is designed to facilitate the diagnosis of common mental disorders in primary care patients [18]. The PHQ is a self report version of the Primary Care Evaluation of Mental Disorders (PRIME-MD). The questions do not only focus on mood disorders but also about functional impairments, life stressors and specific events (such as menstruation, pregnancy and childbirth). Its diagnostic validity is good, and patients feel comfortable filling in the questionnaire [19]. There is a 15-item questionnaire for men and a 16-item questionnaire for women, and the scoring range varies. We consider that a decrease in the score on this questionnaire after the intervention represents a reduction in mood disorders, functional impairments, life stressors and distress about specific events.

#### Improvement in problem-solving skills

The Social Problem Solving Skills-Revised (SPSI-R, 15) is a 52-item, self-report inventory, which is designed by D'Zurilla to measure problem-solving skills [20]. The SPSI-R consists of five factors: 1) positive problem orientation (PPO), 2) negative problem orientation(NPO), 3) rational problem solving (RPS), 4) impulsivity/carelessness style (ICS) and, 5) avoidance style(AS). Alphas for these five scales range from .76 to .92 [21] an test-retest reliability ranges from .72 to .88 [20].

#### Psychological and physical well-being

This will be measured with the Short Form-36 (SF-36) which contains 36 questions and standardized response options and relating to eight different areas (multi-item): physical functioning, role limitations due to psychical health problems, bodily pain, general health perceptions, vitality, social functioning, role limitations due tot emotional problems, and general mental health [22]. The mean alpha for reliability in the general population is good, as well as validity which makes the SF-36 a practical instrument for use in the general population.

#### Social support

The Social Support Inventory is a questionnaire which comprises 20 descriptions of social support pertaining to emotional support, informative support, social companionship, or instrumental support. Together these items give an overall representation of satisfaction with social support (the perceived adequacy). It is a reliable and brief measurement instrument which is not influenced by psychological distress [23].

#### Coping-styles

The Ways of Coping Questionnaire (WAYS) (the Dutch adaption is called the VOMS: Vragenlijst over Omgaan met Situaties) is based on the Lazarus and Folkman transactional coping theory of [18]. It measures coping processes, not coping dispositions or styles. The WAYS can assess and identify thoughts and actions that individuals use to cope with stressful encounters in everyday life. The WAYS measures eight coping factors: confrontive coping, distancing, self-controlling, seeking social support, accepting responsibility escape-avoidance, planful problem solving, and positive reappraisal.

##### Rumination

Actual scientific reports suggest that rumination is a significant, and probably prognostic, factor for depression. The rumination scale (RRS) measures the extend to which people ruminate [24]. Rumination is seen as a coping style and characterizes depressive mood. The reliability is good and its validity is satisfying [25,26].

#### Problem evaluation

This will be assessed with a brief, qualitative questionnaire about medical outcomes, the care, the illness and the treatment of the patients, as experienced by the patients, to complement all the quantitative questionnaires. We chose the PSYCHLOPS(also known in the literature as MYMOP [27,28]) to evaluate the problems patients experience and the progress they make over time.

#### Health care utilization

The Trimbos/iMTA questionnaire for Costs associated with Psychiatric Illness (Tic-P) is used to measure the amount of health care received by the patients and to register sickness absence from work [29] Furthermore, we chose the EQ-5D (or Euroqol, [30]) because this is a standardized measurement instrument for a wide range of health conditions which provides a simple descriptive profile and a single index value for health status. The EQ-5D (or EuroQol) was originally designed to complement other instruments such as the SF-36, and it is administered to assess a patient's general health status, in 5 dimensions: mobility, self-care, usual activities, pain/discomfort and anxiety/depression[1]. Because each of the five dimensions can be sub-divided into 3 levels a total of 243 health states can be assessed. Using the Dolan model (1997) the total score will be expressed in utilities [31]. The official Dutch translation of the Euroqol will be administered [31,32]. Incremental cost-effectiveness ratios will be calculated, in which the difference in costs between intervention subjects and control subjects will be divided by the difference in effects between both groups. Incremental cost-utility ratios will also be calculated in which the difference in costs between the two groups will be divided by the difference in QALYs gained between the two groups.

### Power/analysis

Randomization takes place at patient level. To evaluate the effects of the randomization, descriptive statistics will be used to compare the baseline measurements of the two groups. If necessary, differences between baseline variables on relevant characteristics (such as baseline HADS score) will be entered as covariates in the analysis.

To detect a clinically relevant difference between interventions (effect size of 0.4) with the primary outcome measure HADS (power of .90 and an alpha of .05) 130 completers are needed. In both conditions there will be 65 completers. We estimate the drop-out rate to be on 20%, so we therefore need 160 participants. If 20 practices cooperate, we will need to include 8 patients in every practice. We expect a non-response of 50%, so we will need to screen 16 patients in every practice. In a sample of patients with mixed symptoms of anxiety and depression, Cropper et al. [33]observed a mean overall HADS score of 6.25 at baseline. In the Dutch validation [16] the primary care patients have a mean on anxiety of 6.2 (SD 3.8) and 3.7(SD 3.4) for depression with a total mean of 9.9 (SD6.1). We consider a standardized mean difference (SMD) of 0.4 (p = 0,05) on the primary outcome (HADS) to represent a relevant improvement in the PST group versus the usual care group[34].

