#### Analysis

Linear regression models will be used to examine differences in investigate on the HADS. Scores will be entered in a repeated measure design (GLM), and (optional) covariates will be differences at baseline level. Repeated measures with several independent variables will be used to investigate differences in improvement in all secondary outcome measures between groups. The analyses will be performed on a per protocol basis ('completers'), as well as according to the 'intention-to-treat' principle. Trend analyses will also allow 'last observation carried forward' analyses. To assess whether protocol deviations have caused bias, the results of the intention-to-treat analyses will be compared with analyses of the PST group, including the completers.

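### Baseline HADS enters the primary model only if the arms look unbalanced; adjusting for it unconditionally is more precise and fixes the model in advance

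*Protocol article*

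**What the plan says.** The Power/analysis section of the protocol article sets out a two-step rule. First the arms are compared: "To evaluate the effects of the randomization, descriptive statistics will be used to compare the baseline measurements of the two groups". Then the model is settled: "If necessary, differences between baseline variables on relevant characteristics (such as baseline HADS score) will be entered as covariates in the analysis".

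The Analysis section describes the HADS model in the same spirit: "Scores will be entered in a repeated measure design (GLM), and (optional) covariates will be differences at baseline level". Neither section commits to baseline HADS in the primary model. Nor does the Analysis section say whether baseline is one of the repeated levels.

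The score itself will be available, because the Design section has every patient complete a baseline questionnaire: "At baseline, after the intervention and after 3 and 9 months the patients will be asked to fill in a questionnaire". The sample-size paragraph uses a plain standardised difference of 0.4 and contains no term for the correlation between baseline and follow-up.

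**The concern.** Randomisation is by patient and allocation is concealed, so any difference between the arms at baseline is chance. Testing or inspecting that difference says nothing about whether baseline HADS is worth including. It is worth including because a patient's score at entry is expected to predict the later score, and the variance it removes is removed whether the arms are balanced or not.

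Under the stated rule, the usual outcome of a sound randomisation (arms that look alike) is that baseline HADS is not a covariate. Two things are at stake:

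- **Precision.** A score already collected from everyone is not put to its best use.
- **A fixed model.** The primary model is not settled until data have been examined. The section on arguments for publishing a design presents prior publication of the analysis plan as a guard against analysis bias, and a conditional covariate rule weakens that guard.

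**Working it through.** **Inputs from the protocol article (Power/analysis).** Effect size: "We consider a standardized mean difference (SMD) of 0.4 (p = 0,05) on the primary outcome (HADS". Design targets: "power of .90 and an alpha of .05) 130 completers are needed". Arm size: "In both conditions there will be 65 completers". Sidedness is not stated; two-sided is assumed.

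**Input not in the document.** The baseline-to-follow-up correlation r. It is assumed to lie between 0.3 and 0.7.

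**The plan's own figure.** For two independent means, n per arm = 2 × (1.960 + 1.282)² / 0.4² = 131.3, so 132 per arm and 264 in total. The stated 130 in total is not reproduced. At 65 per arm the noncentrality is 0.4 × √(65/2) = 2.28 and power is 0.62. That is a separate sample-size matter; here it only sets the starting point.

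**Three uses of baseline, one follow-up score, 65 per arm, noncentral t.** With equal variances at baseline and follow-up, the effective standardised difference is:

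- baseline left out: 0.4
- baseline as covariate (ANCOVA): 0.4 / √(1 − r²)
- change score: 0.4 / √(2(1 − r))

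| Assumed r | Left out: power | Covariate: effective SMD | Covariate: power | Change score: effective SMD | Change score: power |
|---|---|---|---|---|---|
| 0.3 | 0.62 | 0.419 | 0.66 | 0.338 | 0.48 |
| 0.5 | 0.62 | 0.462 | 0.74 | 0.400 | 0.62 |
| 0.6 | 0.62 | 0.500 | 0.81 | 0.447 | 0.72 |
| 0.7 | 0.62 | 0.560 | 0.89 | 0.516 | 0.83 |

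The ordering does not depend on the value of r. The variance ratio of ANCOVA to the unadjusted comparison is 1 − r². The ratio of ANCOVA to the change score is (1 − r²) / (2(1 − r)) = (1 + r)/2. Both are below 1 for any r strictly between 0 and 1.

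**What a conditional rule does.** The article gives no criterion, so one was assumed: adjust only if the baseline comparison has p < 0.05, and otherwise leave baseline out. In 100,000 simulated trials with 65 per arm:

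| Assumed r | Power, conditional rule | Power, always adjusted | Type I error, conditional rule |
|---|---|---|---|
| 0.5 | 62.8% | 73.8% | 4.3% |
| 0.7 | 63.6% | 88.3% | 3.5% |

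Such a rule keeps almost none of the gain, and its type I error is below 5%. In the same simulation, taking the smaller of the adjusted and unadjusted p-values after seeing both gave a type I error of 7.3% (r = 0.5) and 8.2% (r = 0.7).

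**The case against.** The strongest reply is that an unadjusted test at one follow-up is not what the article plans. It plans a repeated-measures GLM, the primary outcome is a reduction in symptoms, and baseline is the first of four questionnaires. Baseline may well be one of the repeated levels, with the group-by-time term as the test. Baseline is then already used, much as in a change score. This stands: a reader might infer from the 0.62 and 0.89 that the plan throws away 27 points of power at r = 0.7, and the document does not support that. On the change-score reading the gain at r = 0.7 is about 5 points. Adjustment is still better at every r examined, and at r = 0.3 the change score does worse than ignoring baseline.

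Using all three follow-ups also raises the starting point. Under compound symmetry with a constant effect (normal approximation), the mean of three follow-up scores gives 87.7% to 68.8% power without baseline for r from 0.3 to 0.8, against 92.9% to 99.8% with it as a covariate. So 0.62 is not established as the trial's power under its own model.

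A reader might also infer that the rule inflates type I error. The plan describes looking at baseline data, not outcomes, and a fixed imbalance rule is conservative. Inflation needs the open trigger to be used to choose between models after results are known, which the article nowhere describes.

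Finally, the exact criterion for adjusting is a detail that a condensed article may leave to a fuller plan. Its absence is not the point; the principle of adjusting because of imbalance is stated, and that is what is wrong.

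**Conclusion.** The point holds as a low-cost improvement to the analysis. The article ties adjustment for baseline HADS to observed imbalance, which is the wrong reason for adjusting, and so leaves the primary model conditional on the data.

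With one follow-up score, 65 per arm and SMD 0.4, always adjusting gains about 4, 12, 19 and 27 points of power over leaving baseline out, at r of 0.3, 0.5, 0.6 and 0.7. Over a change-score use of baseline it gains about 18, 12, 9 and 5 points. Which comparison applies cannot be settled from the text. The direction is secure; the size rests on an assumed r, a two-sided test, equal variances over time and a single follow-up.

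It would go too far to treat adjustment as the cure for the sample size. On one follow-up score, 65 per arm reaches 90% power only if r is about 0.71 and baseline is always in the model, and the article gives no value of r.

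**What to change.** Replace the conditional wording in Power/analysis and the optional wording in Analysis with:

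*The HADS scores after the intervention and at 3 and 9 months are the outcomes in the repeated-measures model; baseline HADS total is a covariate whatever the baseline comparison shows, and is not also an outcome level. Each secondary scale is adjusted for its own baseline value in the same way. No covariate is added or dropped because of observed imbalance.*

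Keep the baseline table as description only. Saying that baseline is not also an outcome level matters. If it were both, its residual variance would be zero, which breaks the sphericity assumption of the univariate test. A group effect averaged over four time points would also be only three quarters of a constant post-treatment effect.

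The cost is a wording change and one degree of freedom. No new data are needed. The sample-size figure needs its own correction.

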### Strengths and limitations

Many methodological requirements for a high quality trial are met [36]. Allocation is concealed through block-randomization by an external researcher. Recruitment of responders will be in the GP's waiting room, without the GP knowing where and how randomization will take place. The methodology used in this trial will overcome concerns of selection bias. The relevance to the Dutch primary care seems sufficient and the generalisability of our sample to patients in everyday practice seems high. The sample size is large, when compared to other trials on psychological problems in general practice [37]. Additionally, whether the outcome is negative or positive, the project will give a clearer understanding of who might or might not benefit from this treatment.

Another strength of this study is the chosen primary outcome, the self-report HADS. The HADS is a well-known questionnaire to measure reduction of symptoms of anxiety and depression. Many previous trials in psychiatry have relied on assessments of the therapist. Another strength is the combination of quantitative assessments and a qualitative process evaluation. If the psychiatric symptoms decline more in the intervention group than in the usual care group, we can therefore safely attribute this to PST treatment. If not, we will explore mechanisms This will provide useful information about implementing the intervention. A practical strength of the study is that the intervention can take place without disturbing care as usual, both in the study as in future implementation.

Some limitations of the present study need to be addressed. It is possible that patients are less motivated to attend PST treatment since screening of all participants takes place in the waiting room of the GP's. This may be lead to a higher dropout percentage in the PST-condition in comparison with the dropout percentage of the CAU.

This study may be criticized because of the lack of a control group without treatment. However, patients are always free to visit their general practitioners. Furthermore, naturalistic studies of the longitudinal course of anxiety and depression indicate that patients who have these symptoms longer than three months are suffering from chronic symptoms [38,39].

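### 130 completers (65 per arm) do not give 90% power for a standardized difference of 0.4 on the inputs stated; a two-group comparison needs about 133 per arm

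*Protocol article*

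**What the plan says.** The Power/analysis section of the protocol article sets the target: "We consider a standardized mean difference (SMD) of 0.4 (p = 0,05) on the primary outcome (HADS) to represent a relevant improvement", meaning PST against usual care. From this it derives "effect size of 0.4) with the primary outcome measure HADS (power of .90 and an alpha of .05) 130 completers are needed", adds "In both conditions there will be 65 completers", and then allows for attrition: "We estimate the drop-out rate to be on 20%, so we therefore need 160 participants". The Design section gives the same total as a minimum, with 80 patients in each arm.

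Randomization is by patient. Sidedness is not stated. The sample-size statement mentions no correlation between repeated scores, no number of measurements and no variance reduction from covariates.

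The Analysis section plans to enter the HADS scores in a repeated-measures general linear model. Questionnaires are given at baseline, after the intervention, and at 3 and 9 months. Baseline differences enter as covariates only if judged necessary (Power/analysis), and the Analysis section again calls them optional.

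**The concern.** The effect is already standardized, so effect size, alpha, power and allocation are all that a two-group sample-size formula requires. The article supplies them, and the usual formula gives about twice the stated number.

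This matters for reading the result. The article treats 0.4 as the smallest relevant improvement and says in its Discussion that the findings may either confirm PST's effectiveness or call it into question. A reader who accepts 90% power will take a non-significant result as fairly strong evidence against an effect of 0.4. If power is materially lower, that reading is too confident. The article also says that it publishes the design so that readers can judge its methodological quality, and the power figure is part of what they will judge.

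**Working it through.** **Inputs (Power/analysis):** SMD d = 0.4; alpha = .05; power = .90; 1:1 allocation; 65 completers per arm. Two-sided testing is assumed, and one-sided is also tried.

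**1. Trying to reproduce 130.** Per arm, n = 2(z_alpha + z_power)² / d².

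- Two-sided, 90%: 2(1.960 + 1.2816)² / 0.16 = 131.3, so 132. The t-test gives 132.3, so 133 per arm and 266 in total.
- One-sided, 90%: 108 per arm, 216 in total.
- Two-sided, 80% (normal formula): 99 per arm, 198 in total.
- One-sided, 80%: 78 per arm, 156 in total.

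None gives 130 in total. Without the factor 2 for two groups, (1.960 + 1.2816)² / 0.16 = 65.7, which is close to the stated 65 per arm.

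**2. Power with 65 per arm, one time point, no adjustment.** The noncentrality is 0.4 × √(65/2) = 2.280. The normal approximation gives Φ(2.280 − 1.960) = 0.626, and the noncentral t gives 0.619. One-sided power is 0.733. If all 80 randomized per arm were analysed, two-sided power would be 0.710.

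**3. Effect detectable with 65 per arm.** (1.960 + 1.2816) × √(2/65) = 0.569, or 0.573 by the t-test, at 90% power; 0.495 at 80%. On the HADS total SD of 6.1 that the article quotes, 0.4 is 0.4 × 6.1 = 2.4 points and 0.573 is 3.5 points.

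**4. Could the repeated-measures model supply 90%?** The plan gives no correlation, so r is an assumption here. Also assumed are compound symmetry and an SMD of 0.4 at each of the three follow-ups. Variance factors relative to a single score are:

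- adjusted mean of three follow-ups: (1 + 2r)/3 − r²
- unadjusted mean of three: (1 + 2r)/3
- mean of three minus baseline: (1 + 2r)/3 + 1 − 2r
- single follow-up adjusted for baseline: 1 − r²

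Power with 65 per arm (noncentral t, two-sided .05, effect 0.4/√factor):

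| Analysis | r = 0.3 | r = 0.5 | r = 0.7 |
|---|---|---|---|
| Mean of three, baseline-adjusted | 0.92 | 0.94 | 0.98 |
| Mean of three, unadjusted | 0.87 | 0.79 | 0.72 |
| Mean of three minus baseline | 0.65 | 0.79 | 0.95 |
| One follow-up, baseline-adjusted | 0.66 | 0.74 | 0.89 |

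The adjusted mean of three passes 90% throughout this range. The change from baseline passes it only at the high end, and the unadjusted mean nowhere in the range. A single adjusted follow-up needs r of about 0.72.

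**The case against.** The strongest reply is that 62% belongs to an analysis the protocol does not plan. The repeated-measures design itself is not optional; only the covariates are. With three follow-ups and baseline adjustment, 65 per arm gives at least 92% power over the assumed correlations, so the sample may be adequate. The article also condenses a fuller document, where a correlation might be recorded.

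Much of this stands. A reader might infer that the trial simply has 62% power and a 38% chance of missing the target effect. The documents do not support that as an unconditional statement. The reply does not rescue the printed figure, however. The sample-size statement refers to no repeated-measures gain, and the feature that would secure the gain, baseline adjustment, is left open. The missing correlation is not the error; the error is a number that does not follow from the inputs printed beside it.

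Other stronger readings also fail:

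- **A per-arm figure was mistaken for the total.** The numbers resemble this (130 against 132 or 133), but the article does not show how 130 was obtained.
- **The completer count should be 128.** It is true that 160 × 0.8 = 128 and 130/0.8 = 162.5. But 130 is a requirement, not a projection, 160 is a stated minimum, and the gap is within rounding.
- **A null result could not count against PST.** With 65 per arm the 95% half-width on the SMD is about 1.96 × √(2/65) = 0.34, so an observed SMD below about 0.05 would still exclude 0.4.
- **The article is wrong to call its sample large.** That is a comparison with other trials, which this calculation does not contradict.

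**Conclusion.** The point holds in this form: the claim of 90% power with 130 completers for an SMD of 0.4 is not supported by the stated inputs. For a standard two-group comparison the requirement is about 133 per arm (108 one-sided), roughly twice the stated 65. The power at 65 per arm is about 62% (73% one-sided), and 90% is reached only at an SMD of about 0.57. These figures assume equal arms, a single outcome time and no adjustment.

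For the type of model actually planned, power cannot be fixed from the article. Across the change-score, unadjusted-mean and adjusted-mean analyses of the three follow-ups it runs from about 0.65 to 0.98, assuming correlations of 0.3 to 0.7, compound symmetry and a constant effect. The finding is therefore a misstated power justification. It does not show that the trial is necessarily too small.

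**What to change.** Keep the sample size and correct the power paragraph in one of two ways.

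1. **Single-time-point basis.** State that 65 completers per arm give about 62% power for an SMD of 0.4 at two-sided .05, and 90% power for an SMD of about 0.57.
2. **Repeated-measures basis.** Make the baseline-adjusted repeated-measures analysis of the HADS the mandatory primary analysis, removing the option to leave baseline out. Restate the power from that model, giving the assumed within-patient correlation, a plausible range for it, and the follow-ups over which the effect is averaged.

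Under either option, state whether the test is one- or two-sided, and say that a non-significant result will be interpreted from the confidence interval for the difference, set against 0.4.

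The cost is rewording and, under the second option, commitment to one primary model. No extra patients are needed. The drawback is that the stated power may become less favourable.
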